## Abstract

**Background:**

Studies in bipolar disorder (BD) to date are limited in their ability to provide a whole-disease perspective - their scope has generally been confined to a single disease phase and/or a specific treatment. Moreover, most clinical trials have focused on the manic phase of disease, and not on depression, which is associated with the greatest disease burden. There are few longitudinal studies covering both types of patients with BD (I and II) and the whole course of the disease, regardless of patients' symptomatology. Therefore, the Wide AmbispectiVE study of the clinical management and burden of Bipolar Disorder (WAVE-bd) (NCT01062607) aims to provide reliable information on the management of patients with BD in daily clinical practice. It also seeks to determine factors influencing clinical outcomes and resource use in relation to the management of BD.

**Methods:**

WAVE-bd is a multinational, multicentre, non-interventional, longitudinal study. Approximately 3000 patients diagnosed with BD type I or II with at least one mood event in the preceding 12 months were recruited at centres in Austria, Belgium, Brazil, France, Germany, Portugal, Romania, Turkey, Ukraine and Venezuela. Site selection methodology aimed to provide a balanced cross-section of patients cared for by different types of providers of medical aid (e.g. academic hospitals, private practices) in each country. Target recruitment percentages were derived either from scientific publications or from expert panels in each participating country. The minimum follow-up period will be 12 months, with a maximum of 27 months, taking into account the retrospective and the prospective parts of the study. Data on demographics, diagnosis, medical history, clinical management, clinical and functional outcomes (CGI-BP and FAST scales), adherence to treatment (DAI-10 scale and Medication Possession Ratio), quality of life (EQ-5D scale), healthcare resources, and caregiver burden (BAS scale) will be collected. Descriptive analysis with common statistics will be performed.

**Discussion:**

This study will provide detailed descriptions of the management of BD in different countries, particularly in terms of clinical outcomes and resources used. Thus, it should provide psychiatrists with reliable and up-to-date information about those factors associated with different management patterns of BD.

**Trial registration no:**

ClinicalTrials.gov: NCT01062607

## Background

Bipolar disorder (BD) is not just a single disorder, but a category of lifelong mood disorders characterised by the presence of one or more recurrent manic, hypomanic and depressive episodes. Individuals who experience manic episodes also commonly experience depressive episodes or symptoms, or mixed episodes in which features of both mania and depression are present. While these episodes are usually separated by periods of normal mood, in some patients depression and mania may rapidly alternate [1].

Estimates for lifetime prevalence of any type of BD range from 0.5% to 5%. However, caution must be used when comparing studies, as the diagnostic assessment methods and criteria used to formulate diagnoses vary from study to study [2]. A recent review of epidemiological studies, which aimed to determine the prevalence of BD in Europe, revealed a remarkable degree of consistency across diverse study designs and between countries. The lifetime prevalence rate of mania (BD type I) appears to be very similar across studies, with estimates ranging from 0.1-0.2% to 1.8%. There is reasonably consistent evidence that BD-I and BD-II disorders, diagnosed according to criteria in the fourth edition of the Diagnostic and Statistical Manual of Mental Disorders (DSM-IV) [1], have an estimated 1-year prevalence of approximately 1%, with no major differences by age group and gender [3].

Over 90% of patients with BD experience recurrences during their lifetime [4], often within 2 years of the initial episode, and the consequences of recurrent illness are substantial for patients. Most randomised controlled trials investigating the efficacy of guideline-based treatment with current drug therapies, or with new emerging therapies, have assessed recurrence in patients who had initially recovered from a mood episode. A further need is to identify the association between patient characteristics and clinical characteristics as predictors of recurrence. This information may allow clinicians to better understand the course of the disease, and to focus on clinical management of those factors with a significant impact on disease outcomes [5].

The emerging picture of the course of BD is quite heterogeneous and includes slow or incomplete recovery from acute episodes, continued risk of recurrences, and sustained morbidity over time, even with continuous long-term use of current treatments. Recovery from an acute episode of mania, even if treatment is established very early in the course of the disorder, may require 3-6 months and thus may no longer meet the standard diagnostic criteria for an acute episode (syndromal remission). Achieving symptomatic remission, defined as the presence of minimal symptoms, may take longer and an 2 additional months may be needed to attain the start of recovery, defined as a sustained remission. Time to remission is even longer following repeated recurrences of BD [6].

Moreover, BD can adversely affect the individual, reducing health-related quality of life and functioning, including employment and productivity at work [7]. It is becoming increasingly recognised that BD is associated with a higher level of functional impairment than previously thought, particularly with regard to social adjustment and vocational functioning [6,7].

In addition to patient burden, caregiver burden is currently one of the key factors in managing patients with BD. The term "caregiver burden" refers to the emotional, social, and financial stresses that caring for a relative or friend with mental illness imposes on the caregiver, and is defined as "the presence of problems, difficulties or adverse events which affect the life of psychiatric patient's caregivers" [8]. On the basis of the method established by Pollak and Perlik [9] the primary caregiver is defined as the family member, friend or significant other who satisfied the greatest number (and at least three) of five criteria, namely: a spouse, parent or spouse equivalent; has the most frequent contact with the patient; helps to support the patient financially; has been the most frequent collateral participant in the patient's treatment; and is the person contacted by treatment staff in case of emergency.

While caregivers can accept some of the burden for the care of patients with BD, management of the disease also places a substantial burden on healthcare providers. BD typically places greater demand on hospital psychiatric services than non-BD depression [10]. A study that permits comparison of different healthcare practices between countries may help to optimise resource utilisation.

One of the key challenges in ensuring that a new study produces meaningful data is to avoid any selection bias in recruitment of both investigators and patients. This can be achieved by having as few exclusion criteria as possible. A further challenge is to recruit patients without contravening the diverse range of laws, which vary within and between countries, covering privacy relating to the acquisition and use of medical data. A recent study in another area of medicine has attempted to avoid investigator bias in patient selection by engaging a third party to manage patient selection and recruitment [11]. In that study, patients were able to opt out without consulting their physician.

In view of the above, the overall objectives of the Wide AmbispectiVE study of the clinical management and burden of Bipolar Disorder (WAVE-bd) study are: to provide accurate and reliable information on the management of patients with BD in conditions representative of everyday clinical practice; to determine the clinical outcomes of such management and the use of resources in relation to the disease; and to establish the factors associated with different management patterns and clinical and functional outcomes.

## Methods

### Study design

The WAVE-bd study (NCT01062607) is a multinational, multicentre, observational, longitudinal or cohort study of patients diagnosed with BD type I or II with at least one mood event in the 12 months prior to the study start (Time 0, Figure 1).

**Figure 1 F1:**
[figure not shown]
**Study design**.

The study comprises two different follow-up phases; one retrospective and one prospective (ambispective design). The retrospective phase for each patient started from the index event, which occurred a maximum of 12 months and minimum of 3 months before Time 0, and ended when the patient signed the informed consent form. Information from medical records related to the patient and their disease during that period (i.e. retrospective information - from index event to inclusion) was recorded in the electronic case report form (eCRF) at the inclusion visit. The prospective phase started when the first patient signed the informed consent form and will end when the last patient included in the study attends their final visit. Data for prospective analysis are collected as described at all visits (including the inclusion visit). All throughout the prospective phase, the required information will be recorded in the eCRF and the questionnaires completed every time the patient attends the psychiatrist's office (unless otherwise stated). The psychiatrist will schedule visits according to real-life clinical practice. No interventions, extra procedures, or extra visits will be required for the purpose of the study.

The study design means that patients will spend variable amounts of time in the study depending on the date of signing the informed consent form, the length of the enrolment period, and the date of their index episode. The minimum time in the study is 12 months and the maximum 27 months, considering the retrospective and prospective phases, and the 6 month enrolment period together (Figure 1).

### Study population

One aim of the study is to determine how patients with BD are managed in different settings and countries (Austria, Belgium, Brazil, France, Germany, Portugal, Romania, Turkey, Ukraine and Venezuela). It is therefore important to obtain a patient population that is representative of real-world practice. The inclusion of sites and patients was determined on that basis.

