### Sites and investigators

Since the type of site is a variable that might influence the management of patients with BD and the profile of patients attending each type of site may be different, it was necessary to select different types of sites to obtain a representative sample. Generally, patients with BD are seen in mental health centres, clinics, private settings, hospitals or specialised units. Since this distribution varies from one country to another, the study centre selection process had to be adapted locally.

Selection of participating sites was based on the percentage of patients that attend different types of sites in each country, thus ensuring that patients attending one specific site type are not over-represented in the study sample (Table 1). These percentages were obtained either from the literature or from expert panels from each participating country.

**Table 1 T1:** Patient recruitment by country and type of study centre

Country	Site type	Patients per site type (%)	Total patients enrolled
Austria	University hospital	16	20
	Private practice	65	81
	General hospital	19	24

Belgium	Clinics	46	190
	Private practice	31	129
	General practitioner	23	95

Brazil	Public hospital	88	146
	University hospital	12	20

France	Hospital/clinics	49	247
	Private practice	51	260

Germany	University hospital	27	59
	Community hospital	21	46
	Private practice	52	114

Portugal	Hospital	24	123
	Private practice	57	295
	Mental health clinic	19	98

Romania	Ambulatory	37	68
	Hospitals	63	115

Turkey	Private practice	39	151
	University hospital	42	162
	State hospital	18	70

Ukraine	Mental health clinic	90	199
	Private practice	10	22

Venezuela	Private practice	33	76
	Public hospital	67	155

The number of participating investigators is sufficient to ensure: 1) that there is a representative sample of the whole psychiatrist population in each country; and 2) inclusion of a sufficient number of patients to provide the required sample size calculated for the study. No other criteria were applied to selection and inclusion of investigators, in order to avoid any selection bias.

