### Statistical analyses

Descriptive statistics will include frequency tables (n, mean, median, standard deviation, minimum and maximum for continuous variables and n, frequency and percentage for categorical values). For the population estimation of the variables, the two-sided 95% confidence interval will be obtained.

In order to assess the association of patient characteristics (including functioning and quality of life status) and clinical management (an independent variable) with clinical outcome variables (clinical evolution, mood events, treatment-related events, suicide attempts, variation in scales), logistic and general linear models have been planned. Interest will focus separately on the management differences between the models or groups of models. Model-based point estimates of odds ratios and corresponding 95% confidence intervals will be reported. P-values will be reported for the comparison between different treatments. Since visit-by-visit information from the study index event is being collected, there will be data on patient status during the whole study period. Therefore, it will be possible to analyse data, relative to the time of mood event initiation.

Cox models for survival outcomes, and mixed models for longitudinal data using country as indicator variables, adjusted for age and gender, have been planned in order to investigate differences in clinical outcomes and related factors between countries. A descriptive analysis has been planned to assess factors related to consumption of healthcare resources and caregiver burden, according to caregiver-reported outcomes.

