### Sample size

The sample size was calculated in order to ensure that the study obtains meaningful data for descriptive purposes of general clinical management and clinical outcomes at a country level. The main outcome used in the sample size calculation was the proportion of episodes in 1.5 years and the goal was to estimate this proportion in the study population. The minimum number of patients required was estimated, based on an expected proportion of patients with episodes in one year of 35%, assuming an alpha = 0.05, power = 0.80 and a precision of 0.05 (with a 95% confidence interval). The estimated sample size was 370 patients per country (or 400 if it is assumed that approximately 10% will be lost to follow up). Fewer patients per country would provide information on the proportion of episodes with a precision less 5%. It was estimated that approximately 3,200 patients across different countries would be included in the study, but that this number might vary depending on the number of participating countries and sample size in each.

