All of the studies described above were based on low rates of recruitment from the eligible population. A total of 3188 randomly selected patients were invited to participate in the WAVE-bd study. Of these, 2965 (93%) accepted the invitation to participate and provided written informed consent. The other 7% of patients screened declined to participate and will not be included in the analysis. The systematic approach to inclusion of patients in the WAVE-bd study and stratification by type of study centre to reflect local practice, combined with the 93% patient acceptance rate, leads us to believe that the study population avoids selection bias and is truly representative of the overall global population with unstable BD. Consequently, the investigators believe that the study promises to provide psychiatrists with reliable and up-to-date information about the factors associated with different management patterns of BD on a global scale.

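### The claim that the sample represents the global bipolar population rests only on within-country features; the ten countries' shares follow no stated population

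*Protocol article*

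**What the plan says.** All references are to the protocol article.

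- **Study population:** "It is therefore important to obtain a patient population that is representative of real-world practice". The context is how patients are managed in different settings and countries. The sentence makes no pooled or global claim.
- **Sites and investigators:** the mix of site types is set separately for each country. Table 1, "Patient recruitment by country and type of study centre", gives the resulting counts. The closing paragraph of the section adds that the data will allow a global view of public against private, academic against standard hospital, and hospital against non-hospital care.
- **Statistical analyses:** "For the population estimation of the variables, the two-sided 95% confidence interval will be obtained". The text does not say whether this interval is pooled or by country. Models comparing countries carry country indicators.
- **Sample size:** the aim is "meaningful data for descriptive purposes of general clinical management and clinical outcomes at a country level", with 370 patients per country, or 400 allowing for about 10% loss. The expected total is about 3,200, and may vary with the number of countries and the size of each.
- **Discussion and conclusions:** 2965 of 3188 invited patients (93%) took part. On the strength of systematic inclusion, stratification by centre type and this acceptance rate, the sample is believed to be "truly representative of the overall global population with unstable BD".

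**The concern.** To represent a population spread over countries, a sample must be sound within each country, and the countries must count in proportion to something defined. The article's design addresses the first condition. The Discussion asserts a conclusion that also needs the second, and none of its supports bears on that. Balancing site types in Portugal, or a high acceptance rate in Austria, says nothing about how many Portuguese patients should stand beside each Austrian one. A large total does not repair the mix either.

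What is at stake is what the study may conclude. The article expects management to vary between countries and plans models to study that variation. If outcomes do differ, any all-country proportion, resource figure or scale mean depends on the country mix. A reader told that the sample is globally representative would take such a figure as a property of the world's patients, when it describes this enrolment. The promised global comparisons of care types carry the same risk.

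**Working it through.** **1. The plan's own figure.** Inputs from Sample size: p = 0.35, precision d = 0.05, 95% confidence.

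- n = 1.96² × 0.35 × 0.65 / 0.05² = 349.6.
- With continuity correction, 349.6 + 1/0.05 = 369.6, so 370. The stated figure is reproduced.
- The stated power of 0.80 plays no part in this formula.

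The 370 is a precision target for one country. It implies no country weights for a pooled figure. Ten countries at 370 would need 3,700, above the roughly 3,200 expected, so country sizes below the target were foreseen.

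**2. Country shares, from Table 1.**

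| Country | n | Share |
|---|---|---|
| Portugal | 516 | 17.4% |
| France | 507 | 17.1% |
| Belgium | 414 | 14.0% |
| Turkey | 383 | 12.9% |
| Venezuela | 231 | 7.8% |
| Ukraine | 221 | 7.5% |
| Germany | 219 | 7.4% |
| Romania | 183 | 6.2% |
| Brazil | 166 | 5.6% |
| Austria | 125 | 4.2% |
| Total | 2965 | |

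The total matches the Discussion. The four largest give 516 + 507 + 414 + 383 = 1820, and 1820/2965 = 61.4%. Portugal has 516/125 = 4.1 times Austria's number. Within countries, the site-type counts match the stated percentages within rounding, so the within-country balance is as described.

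**3. Care-type comparisons.** The private-practice rows sum to 81 + 129 + 260 + 114 + 295 + 151 + 22 + 76 = 1128. France and Portugal supply 260 + 295 = 555 (49%); Brazil and Romania list none. A simple pooled private-practice figure would be half a two-country figure.

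**4. Precision at p = 0.35, on enrolled numbers.**

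- Simple pooled half-width: 1.96 × √(0.2275/2965) = 1.72 points.
- Equal country weights, stratified variance: Σ(1/nᵢ) = 0.04185, so 1.96 × √(0.2275 × 0.01 × 0.04185) = 1.91 points. This agrees with a design effect of 1.24 (effective n about 2390).
- By country: 1.96 × √(0.2275/516) = 4.1 points in Portugal, up to 1.96 × √(0.2275/125) = 8.4 points in Austria.

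**5. How far the country mix could move a pooled proportion.** The documents give no country-specific outcomes and no population weights, so this is illustration only. Assume that the four largest countries share one value and the other six another. Enrolment weighting gives the four a weight of 0.614; equal weighting gives 0.40. The shift is (0.614 − 0.40) × gap.

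| Assumed gap | Shift |
|---|---|
| 0 points | 0 |
| 5 points | 1.1 points |
| 10 points | 2.1 points |
| 15 points | 3.2 points |

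The shift passes the 1.72-point half-width at a gap of 1.72/0.214, about 8 points.

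The answer also depends on the weights. Suppose Belgium, France and Portugal (1437/2965 = 48.5% of enrolment) stood at 25% and the other seven at 45%. Enrolment weighting gives 35.3% and equal weighting 0.3 × 25 + 0.7 × 45 = 39.0%. If those three countries carried between 10% and 60% of the true population weight, the figure would lie between 0.1 × 25 + 0.9 × 45 = 43.0% and 0.6 × 25 + 0.4 × 45 = 33.0%.

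**The case against.** The strongest objection is that no unweighted ten-country estimate is planned. The study is sized for country-level description, its stated estimation goal is modest ("the goal was to estimate this proportion in the study population"), and the between-country models carry country indicators. Weights for a pooled descriptive figure are commonly left to a full protocol or analysis plan, which is not shown. The disputed sentence is in the Discussion, is phrased as a belief, and fixes no estimator or interval.

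Most of this stands, and it rules out three stronger readings.

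- A reader might infer that pooled estimates will weight countries by enrolment. The Statistical analyses section does not say so, and missing standardisation wording in a condensed article is not an error.
- A reader might infer that the pooled interval fails to cover the figure under any defined weighting. The working shows otherwise: at a 5-point gap, the 1.1-point shift against equal weights lies inside the 1.72-point half-width. The split into four large and six small countries also puts the whole difference on enrolment size; if outcomes are unrelated to enrolment size, the shift falls towards zero.
- A reader might infer that a common target of 370 implies equal weights. It is a precision requirement, and equal weights correspond to no patient population either.

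The objection does not rescue the Discussion sentence. That sentence affirms a property of the sample, and every support offered for it operates below the level of the country mix.

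**Conclusion.** The concern holds as a point about what may be concluded. The design can support a claim of representativeness within each participating country, to the extent that its site-type balancing and systematic inclusion worked. It cannot support the claim for the global population, because country shares of 4.2% to 17.4%, with 61.4% from four countries, follow no stated population. The share figures come straight from Table 1 and rest on no assumption.

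The numerical consequence is not established. It is zero if countries do not differ, and about 1.1 to 3.2 points for the assumed 5- to 15-point gaps when enrolment weighting is set against equal weighting. No sample-size figure is shown to be wrong by this point.

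**What to change.** - In Discussion and conclusions, limit the claim to patients within each of the ten participating countries and remove the reference to the global population. Qualify the promise of global care-type comparisons in Sites and investigators in the same way.
- Keep country-specific estimates as the main descriptive result, in line with the Sample size section. Their half-widths at 35% are 4.1 to 8.4 points on enrolled numbers.
- Describe any ten-country figure as a summary of the enrolled sample, or give it with declared country weights and a country-stratified variance. Equal weights are one illustrative option; population weights would need a cited source.

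The cost is wording and a small amount of analysis, with no new data. Under equal weights, the pooled half-width at 35% widens from 1.72 to 1.91 points.
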